# A phase II randomized trial of Observation versus stereotactic ablative RadiatIon for OLigometastatic prostate CancEr (ORIOLE)

**DOI:** 10.1186/s12885-017-3455-6

**Published:** 2017-06-29

**Keywords:** Prostate cancer, Stereotactic body radiation therapy, Stereotactic ablative radiotherapy, Oligometastasis

## Abstract

**Background:**

We describe a randomized, non-blinded Phase II interventional study to assess the safety and efficacy of stereotactic ablative radiotherapy (SABR) for hormone-sensitive oligometastatic prostate adenocarcinoma, and to describe the biology of the oligometastatic state using immunologic, cellular, molecular, and functional imaging correlates. 54 men with oligometastatic prostate adenocarcinoma will be accrued. The primary clinical endpoint will be progression at 6 months from randomization with the hypothesis that SABR to all metastases will forestall progression by disrupting the metastatic process. Secondary clinical endpoints will include local control at 6 months post-SABR, toxicity and quality of life, and androgen deprivation therapy (ADT)-free survival (ADT-FS). Further fundamental analysis of the oligometastatic state with be achieved through correlation with investigational ^18^F–DCFPyL PET/CT imaging and measurement of circulating tumor cells, circulating tumor DNA, and circulating T-cell receptor repertoires, facilitating an unprecedented opportunity to characterize, in isolation, the effects of SABR on the dynamics of and immunologic response to oligometastatic disease.

**Methods/design:**

Patients will be randomized 2:1 to SABR or observation with minimization to balance assignment by primary intervention, prior hormonal therapy, and PSA doubling time. Progression after 6 months will be compared using Fisher’s exact test. Hazard ratios and Kaplan-Meier estimates of progression free survival (PFS), ADT free survival (ADT-FS), time to locoregional progression (TTLP) and time to distant progression (TTDP) will be calculated based on an intention-to-treat. Local control will be assessed using Response Evaluation Criteria in Solid Tumors (RECIST) 1.1 criteria. Withdrawal from the study prior to 6 months will be counted as progression. Adverse events will be summarized by type and grade. Quality of life pre- and post- SABR will be measured by Brief Pain Inventory.

**Discussion:**

The ORIOLE trial is the first randomized, non-blinded Phase II interventional study in the North America evaluating the safety and efficacy of SABR in oligometastatic hormone-sensitive prostate cancer. Leading-edge laboratory and imaging correlates will provide unique insight into the effects of SABR on the oligometastatic state.

**Trial registrations:**

ClinicalTrials.gov Identifier: NCT02680587.

URL of Registry: https://clinicaltrials.gov/show/NCT02680587

Date of Registration: 02/08/2016.

Date of First Participant Enrollment: 05/23/2016.

## Background

Cancer is the second leading cause of death in the United States, chiefly from an inability to control metastatic disease. Systemic therapy alone is not curative for patients with most metastatic solid tumors [1]. The metastatic capacity of cancers behaves along a spectrum of disease progression, such that some tumors have spread widely before clinical detectability and others rarely if ever metastasize. The presence of an oligometastatic state, at which point metastases are limited in number and location, was originally proposed by Hellman and Weichselbaum, who suggested that these patients would benefit from effective local therapy in addition to systemic therapy [1].

The treatment of metastases depends on multiple factors including 1) the location of the primary tumor, 2) the size, number and location of metastases, 3) the availability and effectiveness of therapies (e.g. surgery, radiation, and chemotherapy), and 4) the patient’s functional status. Conventional moderate dose radiation for metastatic disease is given primarily for palliation, but recent advances in radiation delivery now make it possible to image and treat precisely within any anatomic region of the body [2, 3]. As a result, highly accurate radiation at tumorocidal doses can be delivered in 1 to 5 outpatient treatments [4–8].

Stereotactic radiation therapy entails highly conformal and precisely targeted radiation delivered in a very dose intensive fashion. In the brain, this approach (termed stereotactic radiosurgery or SRS) has been shown to be a highly effective treatment for brain metastases [9]. Data suggests that select small extracranial tumors (either primary or metastatic tumors) may be effectively controlled using a similar approach known as stereotactic body radiotherapy (SBRT) or stereotactic ablative radiotherapy (SABR). Local control in excess of 75% has been reported for metastatic tumors of the spine, lung and liver, which is significantly higher than standard conventional moderate dose radiation [5, 7, 8, 10–23]. Toxicity has been minimal in multiple U.S., European, and Japanese trials of SABR to the lung, liver, spine, pelvis and abdomen despite the use of very high biological equivalent doses for patients with both organ-confined and metastatic cancer.

The natural history of hormone sensitive oligometastatic prostate cancer is under studied. However, much is known regarding the preceding state of biochemically recurrent prostate cancer that has failed primary treatment. The management of this heterogeneous group of men with a rising PSA often involves relatively long periods of observation until metastases develop at which time the initiation of androgen deprivation therapy (ADT) is typically recommended. Although not entirely appropriate for all men with biochemical failure, data would suggest stalling initiation of ADT is not likely overtly detrimental to overall survival [24]. In the modern era with conventional imaging, oligometastatic hormone sensitive prostate cancer likely comprises a large number of men, possibly the majority of men following failed primary therapy [25–28]. Assuming these men are at a potentially curable state before castration-resistance develops, we need additional treatment strategies to re-examine this large cohort of men.

Based on this emerging evidence, we propose a phase II study of SABR in patients with oligometastatic hormone sensitive prostate cancer. This study is designed to determine if we can improve the outcome of prostate cancer in these men and also to advance the basic understanding of the oligometastatic state as it pertains to signaling dynamics, cell biology, and immunologic responses. Clinically, we anticipate that SABR in the oligometastatic setting will safely forestall disease progression, thereby lengthening the time before initiation of hormonal therapy and protecting patients from the known deleterious side effects of this conventional systemic approach and thus improve quality of life [24].

As we continue to refine the standard approaches to treatment of oligometastatic cancer within and beyond the prostate, principle questions remain unanswered which may greatly enhance our collective ability to improve patient outcomes. Chief among these are how best to identify patients in the oligometastatic state, and what aspects of this state differentiate it fundamentally from patients with organ-confined or polymetastatic disease. To address the former, PET/CT imaging utilizing the investigational prostate specific membrane antigen (PMSA) targeted radiotracer, ^18^F-DCFPyL, will be compared to conventional bone scan and CT imaging to assess the utility of this imaging test in identifying oligometastases before SABR and monitoring disease response following SABR [29–31]. Alterations in the biology of the oligometastatic state induced by SABR will be investigated using leading-edge correlatives, including: analysis of circulating tumor cells (CTCs; Epic Sciences, San Diego, CA), deep sequencing of circulating tumor DNA (ctDNA) using Cancer Personalized Profiling by deep sequencing (CAPP-Seq) to non-invasively assess tumor burden, and ImmunoSEQ profiling of T-cell repertoires to elucidate the immunological response to SABR (Adaptive Technologies, Seattle, WA). Finally, use of the Color Genomics platform (Burlingame, CA), a hereditary cancer assay assessing pathogenic mutations in 30 cancer predisposition genes that account for >90% of the germline mutations known to occur in men with castrate resistant metastatic prostate cancer (mCRPC), will inform efforts to advance a more personalized medicine approach to tailor screening and therapies to these men [32, 33].

## Methods/design

This study was approved by the Reaserach Ethics Boards of Johns Hopkins Medicine. The ORIOLE Trial is registered at the US National Institutes of Health (ClinicalTrials.gov) # NCT02680587 and Current Controlled Trials IND/IDE Number: 121064.

### Objectives

Primary endpoint: to determine the proportion of men with oligometastatic hormone sensitive prostate cancer who have progressed after 6 months from randomization to observation *versus* SABR.

#### Secondary endpoints

To describe the toxicity of SBRT/SABR delivered for the population enrolled using Common Terminology Criteria for Adverse Events (CTCAE) version 4.0.To determine local control at 6-months after SABR in patients with oligometastatic disease.To assess progression free survival (PFS) and ADT-free survival (ADT-FS) after randomization defined as the time interval between the day of randomization and progression.To assess quality of life in the SBRT/SABR arm using the Brief Pain Inventory form [34].To estimate the proportion of ^18^F-DCFPyL-PET/MRI or –PET/CT positive sites that are positive for new or progressive metastatic disease by bone scan/CT at baseline and 6 months following SABR and vice versa.To enumerate CTCs using EPIC HD-CTC platforms at baseline and day 180 from randomization.To enumerate circulating tumor DNA (ctDNA) using Cancer Personalized Profiling by deep sequencing (CAPP-Seq) at baseline, day 90 and day 180 from randomization for control and SABR arms.To quantitatively sequence T-cell receptor (TCR) repertoires using peripheral blood monocytes and the ImmunoSEQ platform at baseline and day 90 from randomization.

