### Evaluation of randomization and blinding

This study will employ a randomized phase II design to determine the appropriateness of a subsequent phase III trial based on comparison of rate of progression at 6 months. An interactive web response system (IWRS) will be utilized to obtain the patient’s randomization assignment. Randomization will occur in a 2:1 fashion for SABR and observation arms, respectively. A minimization approach [35] will be applied to ensure balanced assignment to each treatment arm by: 1) Initial treatment with surgery vs. radiation therapy; 2) Prior hormonal therapy vs. no prior hormonal therapy; and 3) PSADT <6 mos vs. 6-14.9 mos. The on-study date for protocol entry will be the day that the study subject is randomized. Patients will be re-evaluated for radiographic response 6 months after randomization. Trial radiologists evaluating for treatment responses will be blinded to the treatment group and treatment specifics. The trial radiologists and the principal investigator will be unblinded only if a patient progresses at any time during the study.

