Site-specific grade 4/5 toxicity will be monitored in the SABR arm. If it becomes evident that the proportion of grade 4/5 toxicity at specific sites convincingly exceeds 20%, the study will be halted for a safety consultation. Specifically, we will apply a Bayesian toxicity monitoring rule that suspends the enrollment for a posterior probability ≥ 75% of toxicity being larger than 20%. The monitoring rule uses Beta (0.5, 5.5) as prior distribution, meaning our prior guess of the proportion of toxicity is 8.3% with a 90% chance that this proportion is 0.04%-30.6%.

Follow-Up:Patients will be followed from Day 1 to Day 180.All AEs and serious adverse events (SAEs) are recorded on source documents. The investigator will follow up on all AEs and SAEs until the events have subsided, returned to baseline or, in case of permanent impairment, until the condition stabilizes.

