### Stastical analysis

#### Sample size and accrual

The primary endpoint will be progression of disease at 6 months. Historical data on this patient population indicate that >80% would show progression, within a 6-month period without treatment, and thus this is the progression rate we expect in subjects in the control/observation arm [37–39]. We hypothesize that SABR will reduce progression at 6 months by 50% [40]. A sample size using a 2:1 randomization scheme of 36 in the SABR arm and 18 patients in the control group will provide 85% power to detect a decrease in relapse rate from 80% to 40% with a type I error = 0.05 using one-sided Fisher’s exact test. Thus, we will accrue a total of 54 patients. Patients withdrawing within one month of enrollment or prior to day 1 of SABR or observation will be replaced.

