#### Data analysis

##### 2.4.2.1.Analysis of primary objective

A minimization approach [35] will be applied to ensure balanced assignment to each treatment arm by: 1) Initial treatment with surgery vs. radiation therapy; 2) Prior hormonal therapy vs. no prior hormonal therapy; and 3) PSADT <6 mos vs. 6-14.9 mos. Baseline PSA level is defined as that measured Day 1 following randomization.The primary clinical outcome will be the proportion of patients who have progressed after 6 months from randomization. For each arm, we will calculate the proportion of patients who have progressed and extract 95% confidence intervals. If a patient has withdrawn from the study before 6 months, they will be considered to have progressed.Progression will be a composite endpoint defined from the Prostate Cancer Working Group 2 (PCWG2) criteria for mCRPC [38] and our previous trials in a population of men with biochemical failure without metastases [37–39]. Progression will be defined as either: 1) a ≥ 25% increase in PSA from nadir (and by ≥ 2 ng/mL), requiring confirmation ≥ 4 weeks later (PCWG2 criteria); and/or, 2) clinical/radiographic-progression defined as symptomatic progression (worsening disease-related symptoms or new cancer-related complications), or radiologic progression (on CT scan: ≥ 20% enlargement in sum diameter of soft-tissue target lesions [RECIST 1.1 criteria]; on bone scan: ≥ 1 new bone lesions), initiation of ADT or death due to any cause, whichever occurs first. Death is considered a severe adverse event here.We will compare the proportion of patients who have progressed in the observation and SABR arms using Fisher’s exact test. The analysis population includes all randomized subjects based on intention-to-treat.

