##### 2.4.2.2.Analysis of secondary objectives

For safety analysis, adverse events will be summarized by type and grade.Hazard rate estimates and 95% confidence intervals as well as Kaplan-Meier (KM) estimates will be calculated for PFS, ADT-FS, TTLP and TTDP. The median PFS, ADT-FS, TTLP and TTDP will be reported.Each metastatic lesion will be considered a target lesion and independently evaluated for response using RECIST 1.1 or bone scan evaluation criteria below. The lesion will be coded as locally controlled if it is considered stable radiographic disease or if there is evidence of a partial or complete response. Local control assessment will start at three months following randomization and continuous assessment will be pursued during the follow-up period. The proportion of locally controlled lesions will be estimated using generalized estimating equations.QoL will be assessed using the Brief Pain Inventory form. An overall score will be calculated pre-treatment and at the time of the 2^nd^ radiologic reassessment. The change in score will be evaluated by paired t-test.

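### ADT-free survival is given the same event as PFS, so as written it cannot measure delay of hormonal therapy; in addition, the SABR-arm median is not expected to be reached by Day 180

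*Protocol article*

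**What the plan says.** The Secondary endpoints section of the protocol article sets the aim "To assess progression free survival (PFS) and ADT-free survival (ADT-FS) after randomization defined as the time interval between the day of randomization and progression". This is the only definition of ADT-FS in the article.

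Section 2.4.2.1 (Analysis of primary objective) defines progression as a composite. Its components are confirmed PSA rise, symptomatic progression, radiologic progression, and "initiation of ADT or death due to any cause, whichever occurs first".

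Elsewhere ADT-FS is treated as an endpoint in its own right:

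- The Abstract lists it among the secondary clinical endpoints and again among the time-to-event analyses.
- Section 2.4.2.2 (Analysis of secondary objectives) says that "Kaplan-Meier (KM) estimates will be calculated for PFS, ADT-FS, TTLP and TTDP" and that "The median PFS, ADT-FS, TTLP and TTDP will be reported". TTLP and TTDP are the times to locoregional and distant progression.
- The Discussion names freedom from hormonal therapy next to disease progression as something the trial will compare.
- The Background gives a longer time before hormonal therapy as an anticipated clinical benefit of SABR.

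On follow-up, the Interventions section states "Patients will be followed from Day 1 to Day 180". For design rates, Sample size and accrual says "Historical data on this patient population indicate that >80% would show progression, within a 6-month period without treatment", and plans for 80% progression on observation against 40% on SABR.

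**The concern.** An endpoint named for freedom from ADT should end when ADT starts or the patient dies. Here it ends at progression, which can occur in a man who has not started ADT and may not start it for some time. The trial would then report two endpoints that are one variable, and the question of how long SABR postpones hormonal therapy would go unanswered.

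If the definition is left and later reinterpreted, the ADT-FS event would be chosen in a non-blinded trial after data have been seen.

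The second, smaller concern is that section 2.4.2.2 promises medians for four time-to-event endpoints, while the design expects most SABR patients to be progression-free when follow-up ends.

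**Working it through.** **1. Do the two endpoints differ as written?** Let PFS be the time to the first of {PSA progression, symptomatic progression, radiologic progression, ADT start, death}, from section 2.4.2.1. ADT-FS as written is the time to progression, which is the same set. ADT-FS in its ordinary sense is the time to the first of {ADT start, death}, a subset.

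| Patient | PFS | ADT-FS as written | ADT-FS ending at ADT or death |
|---|---|---|---|
| PSA progression dated Day 90 and confirmed, no ADT by Day 180 | event, Day 90 | event, Day 90 | censored, Day 180 |
| PSA progression dated Day 90, ADT started later but before Day 180 | event, Day 90 | event, Day 90 | event, at ADT start |
| ADT started with no earlier progression | event, at ADT start | event, at ADT start | event, at ADT start |
| New bone lesion at Day 180, no ADT | event, Day 180 | event, Day 180 | censored, Day 180 |

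The second and third columns agree for every patient. Only the last column carries information about time to hormonal therapy.

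**2. The plan's own figure.** Inputs from Sample size and accrual: 18 observation and 36 SABR patients, 80% against 40%, one-sided Fisher's exact test at 0.05. Exact enumeration over Binomial(18, 0.8) × Binomial(36, 0.4) gives power of 85.06%, against 85% stated. The figure reproduces, so 80% and 40% can be used as the design rates below.

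**3. Where the PFS medians lie.** With 6-month progression probability p, an exponential curve has median 6·ln 2 / (−ln(1 − p)) months.

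- Observation, p = 0.80: 6 × 0.693 / 1.609 = 2.58 months.
- SABR, p = 0.40: 6 × 0.693 / 0.511 = 8.14 months.

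The exponential form is an assumption. With a Weibull curve of shape k through the same 6-month rate, the median is 6·(ln 2 / (−ln(1 − p)))^(1/k).

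| Shape k | Observation (months) | SABR (months) |
|---|---|---|
| 0.7 | 1.8 | 9.3 |
| 1 | 2.6 | 8.1 |
| 1.5 | 3.4 | 7.4 |
| 2 | 3.9 | 7.0 |

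For SABR the conclusion does not depend on shape: an expected 60% progression-free at 6 months lies above 50%.

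**4. Chance of reaching the PFS median by Day 180.** With complete follow-up, the Kaplan-Meier curve reaches 50% when at least half of the arm has had an event.

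- Observation: P(at least 9 of 18 | 0.80) = 99.9%.
- SABR: P(at least 18 of 36 | 0.40) = 14.6%.

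**5. ADT-FS with its own event.** Its events are a subset of the PFS events, so for each patient the ADT-FS time is no earlier than the PFS time. With complete follow-up, the chance of reaching its SABR median is therefore at most 14.6% at the design rate. How much lower it lies depends on how many progressors have started ADT or died by Day 180, which the article does not give. Over an assumed range, the same in both arms:

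| Assumed share of progressors with ADT or death by Day 180 | Observation | SABR |
|---|---|---|
| 100% | 99.9% | 14.6% |
| 75% | 86.5% | 0.9% |
| 50% | 26.3% | <0.1% |
| 25% | 0.4% | <0.1% |

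No rates are given for TTLP or TTDP, so nothing is computed for them.

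**The case against.** **The definition.** It can be said that one definition was compressed over two endpoints, and that the uses of ADT-FS elsewhere show that a separate endpoint was meant. That is probably how the wording arose, but it does not rescue it. If the closing clause applies only to PFS, ADT-FS has no stated event; if it applies to both, they are identical. This is a rule stated wrongly, not detail left to a fuller document. It is fair that the matter concerns a secondary endpoint and that the primary comparison and its power are untouched.

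**The medians.** A reader might infer that 180 days cannot yield the promised medians. The documents do not support that: the plan's own 80% rate puts the observation-arm PFS median well inside follow-up. Nor can one say that the SABR curve never reaches 50%. The 40% is a hypothesis, the chance of reaching the median is about 15% even if it holds, and the chance rises if SABR does less. An unreached Kaplan-Meier median is conventionally reported as such, and the lack of that phrase in an article is not an error.

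**Imaging times.** It is also tempting to argue that conventional imaging after baseline takes place only at Day 180, so that radiologic event times collect on one date. The visit schedule under Interventions lists it only then, and Evaluation of randomization and blinding says "Patients will be re-evaluated for radiographic response 6 months after randomization". But section 2.4.2.2 starts local control assessment at three months and mentions a second radiologic reassessment, and PSA and clinical review also occur at Day 90. The inference is not established. Restricted mean time and interval-censored methods would be preferences, not corrections.

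**Cost.** It might be thought that ADT start is already fully collected through the primary endpoint. Because that composite stops at whichever event comes first, ADT begun after PSA or radiographic progression need not be captured by it. This objection stands and is reflected in the fix.

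**Conclusion.** The definition is wrong as stated. ADT-FS duplicates PFS for every patient and adds nothing about delay of hormonal therapy. This rests on the text alone and needs no numerical assumption.

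The point about medians is secondary and limited to the SABR arm. At the design rate of 40%, the PFS median is not expected by Day 180, and a properly defined ADT-FS median cannot come earlier. The 14.6% assumes complete follow-up and a true rate of 40%; the 8.1 months also assumes an exponential curve (7.0 to 9.3 over the Weibull shapes tried). How far ADT-FS lies beyond PFS cannot be quantified from the document.

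**What to change.** 1. Give ADT-FS its own definition: time from randomization to first ADT initiation or death from any cause. PSA, symptomatic or radiographic progression does not end it, and patients alive without ADT are censored at last contact. Keep the existing definition for PFS only.
2. Record the date of ADT start through Day 180 in every patient, including those who have already met another progression criterion. The medication reviews scheduled at Day 90 and Day 180 in both arms allow this.
3. In section 2.4.2.2, report 6-month Kaplan-Meier estimates with 95% confidence intervals for the time-to-event endpoints, and give a median only where the curve crosses 50%.

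Items 1 and 3 cost wording and analysis code. Item 2 is a small data-collection cost. Sample size, randomization and the primary analysis do not change. The definition should be settled before outcome data are examined by arm.
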